Randomization and blinding will be made using the application Research Randomizer (Social Psychology Network, Middletown, CT, USA) [40] to form the groups. A code consisting of two digits (1 and 2) will be used. The application offers a random list of 30 numbers with digits 1 and 2. This sequence will be carried out remotely by a blind researcher who is not involved in other investigation procedures. After the randomization process, another blind staff member will assign patients among groups. The allocation concealment will be made with closed, sealed, and sequentially numbered envelopes. The evaluators will receive the patients in a different room, ignoring which group they belong to.

To assess the adverse effects, participants will be asked at the end of each session if they experienced effects such as tingling, burning, headache, and drowsiness, among others and the intensity of this sensation. Guidelines for safety on rTMS protocols will be followed [41]. However, no severe adverse effects are expected. Any adverse effect will be notified to a licensed medical doctor. Management of possible adverse effects will be individualized and according to the severity.

Regarding data processing security, data will be recorded separately and will be anonymized and guarded following current European data protection laws. All data will be recorded and verified twice in a database specifically designed for the studies.

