### 2.2. Intervention Protocol

The two intervention protocols have been extracted from previous publications of successful application on upper limb rehabilitation. On the one hand, the investigation by Takeuchi et al. showed significant improvements in those subjects who received bilateral rTMS stimulation (based on the principle of interhemispheric inhibition) [8]. On the other hand, Vourvopoulos et al. published a pilot study using NeuRow, showing a high performance [33].

The intervention will consist of the two therapies administered sequentially on the same day rTMS application before the immersive multimodal BCI-VR training, or just rTMS application, in the control group. The sequence of administration has been decided based on preliminary results of the NeuroMOD project (unpublished) from our group, revealing that patients receiving rTMS prior to NFB had a better performance.

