#### 2.2.1. rTMS Stimulation

Firstly, single-pulse TMS will be performed to acquire a resting motor threshold (rMT). Magstim Rapid2 (Magstim Company, Whitland, Wales, UK) device with an air-cooled 70 mm figure-of-eight magnetic stimulator coil will be used. For all assessments, the magnetic stimulator coil will be placed on M1 in the assessed hemisphere, and a surface electromyogram from the contralateral first dorsal interosseous muscle will be recorded using surface EMG using CED Signal Software (CED, Cambridge, UK). EMG recordings will be recorded and stored in a computer for offline analysis. Stimulation output intensity used to reach the resting motor threshold (RMT) will be used to calculate the parameters for the stimulation sessions.

rTMS parameters will be as described by Takeuchi et al. [8]: 90% of the RMT at 10 Hz, 1000 pulses, 5 s intertrain interval on M1 of the lesioned hemisphere and after 5 min rest period, the contralateral M1 area will be stimulated with 90% of the RMT at 1 Hz, 1000 pulses, with a 50 s intertrain interval. This will be performed in 10 consecutive daily sessions (Monday to Friday).

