Secondly, the BCIs training protocol designed and adapted based on the Graz-BCI paradigm will be used [43]. The first step will be the acquisition of the raw EEG data to extract features to train a classifier to distinguish Right and Left imagined hand movements. Thus, the patient will have to perform mental imagery of the corresponding hand according to the presented stimuli on the screen. The training session will be configured to acquire data in 24 blocks per class (Right-or Left-hand imagery) in a randomized order. Afterwards, the data will be filtered both spatially and temporarily between the Alpha and Beta bands (8–30 Hz) for creating the feature vector.

During the training session, patients will wear a VR headset and see a boat and two high fidelity virtual arms gripping two oars in the first-person view; they will have to imagine the movement of each corresponding hand to rotate each oar and progress, observing the movement imagined on screen [31]. The game interface includes timekeeping and scoring. The goal of the task is to perform as many correct Motor Imagery sequences as possible in a fixed amount of time. To improve adherence, points will be awarded depending on the performance in each session [33,34]. The Motor Imaging training mode will be used. Training sessions will be performed in 12 non-consecutive sessions (Monday, Wednesday and Friday, during four weeks) lasting 30 min each, divided into 3 series of 7 min including initial training and break time to prevent fatigue [31].

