### 2.3. Outcomes Measurement

Three evaluations will be carried out for each patient. A pre-intervention initial evaluation, a second evaluation the week following the end of the rTMS intervention, and a final evaluation after two weeks, when the NeuRow training finish. The first and third evaluation sessions will have an average duration of 120 min, and the second evaluation will have a duration of 60 min (Figure 2).

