**Figure 2 medicina-57-00736-f002:**
[figure not shown]
Schematic representation of intervention protocol. It includes the days of the week and duration of each block of outcomes measurement in pre- and post-evaluation (FMA-UE—Fugl-Meyer Assessment for upper extremity; MI—Motricity Index; SIS—Stroke Impact Scale; RMT—Resting Motor Threshold; NHPT—Nine Hole Peg Test; FTT—Finger Tapping Task; MAS—Modified Asworth Scale; NSA—Nottingham Sensory Assessment; BI—Barthel Index; EEG—Electroencephalogram. Thursday/90–120 min; Monday/60 min; Control Intervention/Monday to Friday/10 rTMS sessions and Experimental Intervention: Monday to Friday/10 rTMS sessions and Monday, Wednesday, and Friday/12 NeuRow sessions).

**Table 1 medicina-57-00736-t001:** Inclusion and exclusion criteria.

INCLUSION CRITERIA	EXCLUSION CRITERIA
Older than 18 years old.	History of seizure or brain aneurysm
Ischemic or hemorrhagic cerebrovascular injury diagnosed by a neurologist and who have at least one brain-imaging test	Pacemakers, medication pumps, metal implants in the head (except dental implants)
Onset of hemispheric ischemic or hemorrhagic stroke >3 months	Clinical instability
Kinesthetic and Visual Imagery Questionnaire (KVIQ) >55.	Muscle tone in the wrist and hand with a modified Ashworth scale (MAS) score equal to or higher than 3 in the wrist
Stability in antispastic medication for more than 5 days	Other pre-existing neurological diseases or previous cerebrovascular accidents with sequelae
Able to read and write	Aphasia
Sufficient cognitive ability to understand and perform tasks: Token Test >11	Previous TMS after stroke Hemispatial neglect (Bells Test >6 omissions on one side) Visual problems
	Flaccid paralysis Brunnstrom’s stage = 1

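### Asking about adverse effects when a session ends gives the experimental arm 16 to 22 scheduled asks over four weeks and the control arm 10 over two, so raw arm-level counts mix NeuRow exposure with more frequent asking

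*Protocol article*

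**What the plan says.** Section 2.1 of the protocol article gives the collection rule: "participants will be asked at the end of each session if they experienced effects such as tingling, burning, headache, and drowsiness", together with the intensity of the sensation. It adds a reporting route, "Any adverse effect will be notified to a licensed medical doctor", and says that rTMS safety guidelines will be followed. The article describes no other scheduled enquiry about adverse effects.

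The sessions differ by arm. Section 2.2 says of the experimental treatment that "The intervention will consist of the two therapies administered sequentially on the same day", with rTMS first, "or just rTMS application, in the control group". The Figure 2 legend gives the schedule: "Control Intervention/Monday to Friday/10 rTMS sessions and Experimental Intervention: Monday to Friday/10 rTMS sessions and Monday, Wednesday, and Friday/12 NeuRow sessions". Section 2.2.1 places the rTMS sessions on consecutive weekdays, and Section 2.2.2 spreads the NeuRow sessions over four weeks.

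Section 2.3 states: "Three evaluations will be carried out for each patient". The first precedes treatment, the second falls in the week after rTMS ends, and the third comes two weeks later, when NeuRow finishes. The measures listed for these visits in Sections 2.3.1 and 2.3.2 and in the Figure 2 legend include no adverse-effect question.

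**The concern.** When a safety question is triggered by attending treatment, an arm with more sessions over a longer period is asked more often and observed for longer. Here the difference is built into the randomized contrast, because NeuRow is the only component that differs in Sections 2.1 and 2.2.

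The effects named in the rule, such as headache and drowsiness, are common and non-specific. In the last two weeks an experimental patient with a background headache has a scheduled occasion to report it, whereas a control patient with the same headache has none unless the evaluation visits carry the question. A table of patients with any adverse effect, by arm, would then combine two things: what NeuRow causes, and what is found because patients are still being asked. A reader of the trial report could not tell them apart.

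**Working it through.** **Inputs.** rTMS: 10 sessions, five weekdays a week, both arms (Section 2.2.1). NeuRow: 12 sessions, three a week for four weeks, experimental arm only (Section 2.2.2). Same-day delivery, rTMS first (Section 2.2). Three evaluations per patient (Section 2.3).

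**Step 1: reproduce the stated counts.**
- rTMS: 5 days × 2 weeks = 10.
- NeuRow: 3 days × 4 weeks = 12.

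Both agree with the Figure 2 legend.

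**Step 2: overlap.** I take both therapies to start in week 1. This fits the same-day rule, and it fits a final evaluation two weeks after the post-rTMS one, when NeuRow ends. Shared days are then 3 × 2 = 6.

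**Step 3: scheduled asks per patient.**

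| Counting rule | Experimental | Control | Ratio |
|---|---|---|---|
| One ask per treatment day | 10 + 12 − 6 = 16 | 10 | 1.6 |
| One ask per therapy session | 10 + 12 = 22 | 10 | 2.2 |
| Per day, plus three evaluations | 16 + 3 = 19 | 10 + 3 = 13 | 1.46 |
| Per therapy, plus three evaluations | 22 + 3 = 25 | 10 + 3 = 13 | 1.92 |

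**Step 4: where the difference falls.**
- Weeks 1 and 2: both arms have 10 treatment days. Asked once a day, this is 10 against 10. Asked after each therapy, it is 10 + 6 = 16 against 10.
- Weeks 3 and 4: the experimental arm has 3 × 2 = 6 NeuRow sessions and the control arm has no treatment session.
- If evaluations count, evaluations 2 and 3 both follow the end of rTMS, so from then on the asks are 6 + 2 = 8 against 2.

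**Step 5: how a raw table responds to the number of asks.** Let p be the chance of a positive answer at each ask, independent between asks and equal in both arms. The documents give no value for p, so a range is assumed. The share of patients with at least one report after k asks is 1 − (1 − p)^k:

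| Assumed p | k = 10 | k = 16 | k = 22 |
|---|---|---|---|
| 1% | 9.6% | 14.9% | 19.8% |
| 2% | 18.3% | 27.6% | 35.9% |
| 5% | 40.1% | 56.0% | 67.6% |
| 10% | 65.1% | 81.5% | 90.2% |

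This shows only that the raw proportion rises with the number of asks. It does not divide the rise between exposure and ascertainment. That would need the background rate of these symptoms, which the documents do not give.

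**The case against.** The strongest reply is that the extra asks follow extra treatment. If a NeuRow session itself causes headache, a patient who has 12 of them truly has more adverse effects, and counting them is right. This stands. A reader might infer from the table above that, at 5% per ask, 67.6% against 40.1% is what the plan would show with no true difference between arms. The documents do not support that, because the model gives each added NeuRow session its own risk. Only background and late effects that are detected unequally are an artefact.

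Two other stronger readings also fail. One is that late effects in controls are never collected. The article is a condensed account and does not call the end-of-session question the sole route, the notification rule has no time limit, and Section 2.3 also uses the word session for evaluation visits. If those count, controls are asked at evaluations 2 and 3. The other is that delayed effects of rTMS are missed in both arms. The question has no stated recall window, and rTMS is given on consecutive weekdays, so an effect that starts in the evening can be reported at the next session.

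It is also true that the article names no safety outcome and no between-arm safety test, so the harm falls on a tabulation and not on a stated analysis. Conventional rehabilitation is given in both arms with no session count. The Abstract and the hypothesis in Section 1 describe the comparator as conventional motor imagery. If controls had imagery sessions their count would rise, but Sections 2.1 and 2.2 and the Figure 2 legend give them none.

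None of this removes the asymmetry. The collection rule and the unequal schedules are both stated, and the ratio exceeds 1 under each way of counting the treatment and evaluation sessions that the article gives.

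**Conclusion.** The point holds as one of unequal ascertainment. As stated, the experimental arm is asked on 16 days, or 22 times if each therapy counts, over four weeks, and the control arm 10 times over two. If evaluations count as sessions, the figures are 19 to 25 against 13. Unless they do count, controls have no scheduled ask in weeks 3 and 4, and background or late effects in that period would be found mainly in the experimental arm.

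The size of the resulting bias cannot be computed from the documents, and part of any excess would be a real effect of NeuRow exposure. The conclusion assumes that both therapies start in week 1 and that controls have no imagery sessions. It concerns any raw safety summary by arm and leaves the efficacy comparison untouched. The change is worth making because it is cheap and cannot be made afterwards.

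**What to change.** Keep the end-of-session question and add the following.

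1. At evaluations 2 and 3, put one identical adverse-effect questionnaire to every patient in both arms, covering the whole interval since the previous evaluation. Have it self-completed or taken by existing staff who do not evaluate outcomes, because the answers could reveal the arm to the blinded evaluators.
2. Base any between-arm safety summary on those two visits, where the number of asks and the period covered are the same in both arms (ratio 1.0).
3. Report session-level effects separately for rTMS and NeuRow, as rates per session delivered.

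The cost is a short form at visits that both arms already attend and a sentence or two of protocol text. No visits or staff are added. The drawback is a longer recall period at the evaluations than at the end of a session. The retained session-level data partly offset this for effects noticed during treatment.

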### 2.2. Intervention Protocol

The two intervention protocols have been extracted from previous publications of successful application on upper limb rehabilitation. On the one hand, the investigation by Takeuchi et al. showed significant improvements in those subjects who received bilateral rTMS stimulation (based on the principle of interhemispheric inhibition) [8]. On the other hand, Vourvopoulos et al. published a pilot study using NeuRow, showing a high performance [33].

The intervention will consist of the two therapies administered sequentially on the same day rTMS application before the immersive multimodal BCI-VR training, or just rTMS application, in the control group. The sequence of administration has been decided based on preliminary results of the NeuroMOD project (unpublished) from our group, revealing that patients receiving rTMS prior to NFB had a better performance.

#### 2.2.1. rTMS Stimulation

Firstly, single-pulse TMS will be performed to acquire a resting motor threshold (rMT). Magstim Rapid2 (Magstim Company, Whitland, Wales, UK) device with an air-cooled 70 mm figure-of-eight magnetic stimulator coil will be used. For all assessments, the magnetic stimulator coil will be placed on M1 in the assessed hemisphere, and a surface electromyogram from the contralateral first dorsal interosseous muscle will be recorded using surface EMG using CED Signal Software (CED, Cambridge, UK). EMG recordings will be recorded and stored in a computer for offline analysis. Stimulation output intensity used to reach the resting motor threshold (RMT) will be used to calculate the parameters for the stimulation sessions.

rTMS parameters will be as described by Takeuchi et al. [8]: 90% of the RMT at 10 Hz, 1000 pulses, 5 s intertrain interval on M1 of the lesioned hemisphere and after 5 min rest period, the contralateral M1 area will be stimulated with 90% of the RMT at 1 Hz, 1000 pulses, with a 50 s intertrain interval. This will be performed in 10 consecutive daily sessions (Monday to Friday).

#### 2.2.2. Immersive Multimodal BCI-VR Training

NeuRow is a gamified BCI training paradigm in VR that allows patients to perform similar motor actions as they would do in real life. NeuRow is rendered through a head-mounted VR headset with 90° horizontal field-of-view and haptic feedback delivered through 2 controllers in both hands.

The paretic limb should be positioned in a resting position on the table. Before setting up the EEG cap plus VR headset in each session, a previous training will be carried out with the following instructions:Ask the patient to perform the rowing movement with both upper limbs with external facilitation of the paretic side.Ask the patient to imagine the movement with eyes closed, focusing on his internal perspective and on the sensation of rotation. Imagine the hand closed in a fist and feel the arm weight and contraction of arm muscles.Imagine the movement slowly and increase their speed.The best strategies will be identified for each participant. The patient reports in detail what he felt/tried to visualize; the researcher will give feedback and will also give a description of the sensation of the movement to the participant during the motor imagination, describing the sequence of movements required for rowing (elbow stretched, closed hand grasping the paddle, etc.).The patient will be asked if he succeeds in imagining the tasks.

It is very important that the movement is natural and biomechanically correct. This training will be carried out daily and prior to the application of the NeuRow system.

Before the actual VR training, the acquisition of the EEG will be carried out. An experienced technician will acquire EEG through a BCIs system with 64 active electrodes equipped with a low-noise biosignal amplifier and a 24 bit A/D converter at 256 Hz (BrainVision actiCHamp biosignal amplifier, Brain Products GmbH, Gilching, Germany). The spatial distribution of the electrodes will cover primarily the motor and somatosensory areas of the brain. Specifically, the Frontal (F3, Fz, F4), Frontal-Central (FC5, FC6), Central (C3, Cz, C4), Central-Parietal (CP5, CP1, CP2, CP6), and Parietal (P3, Pz, P4) in a small Laplacian configuration for spatial filtering (Figure 1). EEG data acquisition and processing will be performed through the OpenVibe platform [42], which will transmit the data via the Lab Streaming Layer (LSL) protocol to control the virtual environment.

Secondly, the BCIs training protocol designed and adapted based on the Graz-BCI paradigm will be used [43]. The first step will be the acquisition of the raw EEG data to extract features to train a classifier to distinguish Right and Left imagined hand movements. Thus, the patient will have to perform mental imagery of the corresponding hand according to the presented stimuli on the screen. The training session will be configured to acquire data in 24 blocks per class (Right-or Left-hand imagery) in a randomized order. Afterwards, the data will be filtered both spatially and temporarily between the Alpha and Beta bands (8–30 Hz) for creating the feature vector.

During the training session, patients will wear a VR headset and see a boat and two high fidelity virtual arms gripping two oars in the first-person view; they will have to imagine the movement of each corresponding hand to rotate each oar and progress, observing the movement imagined on screen [31]. The game interface includes timekeeping and scoring. The goal of the task is to perform as many correct Motor Imagery sequences as possible in a fixed amount of time. To improve adherence, points will be awarded depending on the performance in each session [33,34]. The Motor Imaging training mode will be used. Training sessions will be performed in 12 non-consecutive sessions (Monday, Wednesday and Friday, during four weeks) lasting 30 min each, divided into 3 series of 7 min including initial training and break time to prevent fatigue [31].

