## Abstract

*Background and Objectives:* The motor sequelae after a stroke are frequently persistent and cause a high degree of disability. Cortical ischemic or hemorrhagic strokes affecting the cortico-spinal pathways are known to cause a reduction of cortical excitability in the lesioned area not only for the local connectivity impairment but also due to a contralateral hemisphere inhibitory action. Non-invasive brain stimulation using high frequency repetitive magnetic transcranial stimulation (rTMS) over the lesioned hemisphere and contralateral cortical inhibition using low-frequency rTMS have been shown to increase the excitability of the lesioned hemisphere. Mental representation techniques, neurofeedback, and virtual reality have also been shown to increase cortical excitability and complement conventional rehabilitation. *Materials and Methods:* We aim to carry out a single-blind, randomized, controlled trial aiming to study the efficacy of immersive multimodal Brain–Computer Interfacing-Virtual Reality (BCI-VR) training after bilateral neuromodulation with rTMS on upper limb motor recovery after subacute stroke (>3 months) compared to neuromodulation combined with conventional motor imagery tasks. This study will include 42 subjects in a randomized controlled trial design. The main expected outcomes are changes in the Motricity Index of the Arm (MI), dynamometry of the upper limb, score according to Fugl-Meyer for upper limb (FMA-UE), and changes in the Stroke Impact Scale (SIS). The evaluation will be carried out before the intervention, after each intervention and 15 days after the last session. *Conclusions:* This trial will show the additive value of VR immersive motor imagery as an adjuvant therapy combined with a known effective neuromodulation approach opening new perspectives for clinical rehabilitation protocols.

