Both approaches, the NeuRow training paradigm (NeuroRehabLab, Funchal, Portugal) and bilateral rTMS protocols, are likely to complement their effects, achieving a stronger neuroplasticity enhancement in stroke patients. Both have been used separately for the treatment of motor sequelae in the upper limbs after stroke [8,31,33]. The effects of these combined techniques are not likely to be based only on the increase of cortical excitability but also on subcortical mechanisms.

The efficacy of rTMS and motor imagery has been previously demonstrated, but their combination has not been tested yet. The main objective of this study is to carry out a double-blind, randomized, controlled trial aiming to study the clinical effect of immersive multimodal BCI-VR training using NeuRow system (NeuroRehabLab, Funchal, Portugal) after bilateral neuromodulation with rTMS compared to bilateral rTMS plus conventional rehabilitation in upper limb motor sequelae after subacute stroke (>3 months). We will look for changes in: 1. isometric strength in the upper limb; 2. functional motor scales of the upper limb; 3. hand dexterity; and 4. cortical excitability changes. Our main hypothesis is that multimodal BCI-VR training will be superior to the use of conventional motor imagery as adjuvant therapy to bilateral rTMS.

This protocol combines techniques that have proven to be cost-effective [34]. If it is shown that the clinical improvement with this combination is significant, it will open a new line of combined neuromodulation approaches to reach an effective method for the upper limb motor neurorehabilitation after a stroke.

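### The aim and hypothesis name conventional motor imagery as comparator, but the control arm as described has none, so the arms support only an add-on claim for the NeuRow package

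*Protocol article*

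**What the plan says.** Two statements make conventional motor imagery the comparator. The Abstract aim sets the BCI-VR arm against a control described as "compared to neuromodulation combined with conventional motor imagery tasks". The hypothesis in section 1 is that BCI-VR "training will be superior to the use of conventional motor imagery as adjuvant therapy to bilateral rTMS".

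Four statements define the control without imagery. The objective in section 1 has the new treatment "compared to bilateral rTMS plus conventional rehabilitation in upper limb motor sequelae after subacute stroke". Section 2.1 lists the control group as conventional rehabilitation and bilateral rTMS. Section 2.2 gives controls rTMS only as the study intervention. The Figure 2 legend gives them 10 rTMS sessions and nothing further.

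The experimental package is set out in section 2.2.2. It opens with a preparatory block: "Before setting up the EEG cap plus VR headset in each session, a previous training will be carried out with the following instructions". The first instruction is "Ask the patient to perform the rowing movement with both upper limbs with external facilitation of the paretic side". The next is "Ask the patient to imagine the movement with eyes closed, focusing on his internal perspective and on the sensation of rotation". Identification of good strategies, feedback and verbal description from the researcher, and a check that the patient can imagine the tasks complete the block. The schedule is then stated: "Training sessions will be performed in 12 non-consecutive sessions".

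The Abstract conclusion reads: "This trial will show the additive value of VR immersive motor imagery as an adjuvant therapy combined with a known effective neuromodulation approach". Section 4 repeats it.

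**The concern.** A hypothesis of superiority over conventional motor imagery needs an arm that receives conventional motor imagery. On four of the six statements no such arm exists. A positive trial would then show that adding NeuRow training to rTMS and rehabilitation is better than not adding it, while the stated hypothesis and aim would let it be reported as better than ordinary imagery.

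The conclusion raises a second, smaller problem. It credits VR immersive motor imagery, whereas the package also contains facilitated movement and coached imagery done without a headset. Someone deciding whether immersive equipment is worth buying, when coached imagery needs none, could read the result as an answer to that question. The arms as described do not give one.

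**Working it through.** The plan gives no figure on this point, so the check is a comparison of statements plus a little session arithmetic.

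**1. What controls receive**

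| Place | Control arm | Imagery named? |
|---|---|---|
| Abstract, aim | rTMS and conventional motor imagery | yes |
| Section 1, hypothesis | conventional motor imagery as adjuvant to rTMS | yes |
| Section 1, objective | rTMS and conventional rehabilitation | no |
| Section 2.1 | rTMS and conventional rehabilitation | no |
| Section 2.2 | rTMS only | no |
| Figure 2 legend | 10 rTMS sessions | no |

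Count: 2 with imagery, 4 without. All three places in the methods and figure legend that set out the arms fall on the side without. Section 1 is on both sides, in its objective and its hypothesis.

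**2. What the experimental arm receives beyond that**

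Sessions: 3 per week × 4 weeks = 12, each opening with the preparatory block. The block has 5 instructions: 1 physical (facilitated rowing) and 4 that teach, refine or check imagery. This counts list items and is not a dose.

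Length of the block: a session lasts 30 min and is divided into 3 series of 7 min, so 3 × 7 = 21 min and 30 − 21 = 9 min remain. If the initial training mentioned with that schedule is this block, and it and the breaks lie outside the series, they share 9 min per session, or 12 × 9 = 108 min in all. If it lies inside the series, its length cannot be derived. The wording allows either reading.

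**3. What each version of the control allows**

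- *Control without imagery (four statements).* The arms differ by the whole section 2.2.2 package. The add-on effect of that package can be estimated. Superiority over conventional imagery cannot be tested, because no comparator arm receives imagery. A difference cannot be assigned to VR immersion, because headset-free imagery, assisted rowing and the BCI-VR task arrive together.
- *Control with conventional imagery (two statements).* Superiority of the package over imagery can be tested. It would still be a comparison of the package, preparation included. Whether controls' imagery would be coached in a similar way is not described.

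**4. What the conclusions claim**

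The Abstract conclusion and section 4 name VR immersive imagery. Neither version of the control, as described, isolates it. The Discussion asks a question the arms can answer: whether BCI-VR training enhances the effect of bilateral rTMS.

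**The case against.** The strongest reply is that the package is already defined. The preparatory block sits under the heading of section 2.2.2, so when the hypothesis speaks of multimodal BCI-VR training it means everything in that section, rowing and coached imagery included. Preparation specified for every session is an ordinary part of a complex intervention. The add-on question appears in the section 1 objective, in section 2.1 and twice in the Discussion, and the conclusions themselves speak of additive value. All of this stands. It means the randomised comparison is sound as an add-on contrast, and the block is not a flaw in it.

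A reader might infer something stronger: that the facilitated rowing biases the comparison, or that the plan claims to isolate the equipment from its preparation. The documents support neither. The dose and effect of the rowing are not stated, a negligible contribution is not excluded, and no sentence claims an effect of the headset or EEG interface alone. The phrase in the conclusions is too specific, but it goes no further than that.

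A second reply is that this is a condensed article, so controls may receive imagery that the methods do not describe. That is possible, and nothing here shows that controls get none. But the finding does not rest on silence. It rests on positive statements that disagree: section 2.2 restricts controls to rTMS, and the Figure 2 legend sets the two arms side by side, while the Abstract aim and the hypothesis name imagery. Conventional rehabilitation might also include assisted movement, but section 2.1 gives it to both arms, with the package added in one only.

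**Conclusion.** The point holds as a mismatch between claim and arms. The stated aim and hypothesis cannot be tested against the control arm that four of six statements describe, and the wording of the conclusions is narrower than the package being tested. What the trial can estimate is the effect of the section 2.2.2 NeuRow training programme added to bilateral rTMS and conventional rehabilitation.

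This rests on taking the control arm as those four statements give it, and on conventional rehabilitation, which is not described, not itself supplying the imagery comparator. If controls do receive conventional imagery, the superiority hypothesis becomes testable and the four statements are what is wrong.

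No numerical size of bias follows. The preparatory block supports the attribution point only. The consequence is for what may be concluded, and it should be settled before results are reported.

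**What to change.** Restate the Abstract aim, the hypothesis in section 1, the Abstract conclusion and section 4 in one form: the effect of the NeuRow training programme of section 2.2.2, including its preparatory facilitated movement and coached imagery, when added to bilateral rTMS and conventional rehabilitation.

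Keep the claim of superiority over conventional motor imagery only if controls actually receive it. In that case correct the section 1 objective, section 2.1, section 2.2 and the Figure 2 legend to say so. Claim an effect specific to BCI-VR only if controls also receive the same preparation.

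The restatement costs wording alone and leaves the arms, outcomes, sample size and analysis as they are. Its downside is a narrower claim: the trial would no longer be said to show the separate value of VR immersion or, with controls as the methods describe them, superiority over conventional imagery.
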